#### Self-Compassion Scale

The Self-Compassion Scale [39] is a 26-item questionnaire that measures self-compassion across six subscales named *self-kindness*, *self-judgment*, *common humanity*, *isolation*, *mindfulness*, and *overidentification*. Each item presents a statement with a 5-point response scale ranging from *almost never* to *almost always*. The respondents are asked to answer each statement in terms of how they *typically* act toward themselves in difficult times.

#### Compassion Scale

The Compassion Scale [40] is a 16-item questionnaire that measures compassion for others across four subscales named *kindness*, *common humanity*, *mindfulness*, and *indifference*. Each item presents a statement with a 5-point response scale ranging from *almost never* to *almost always*. The respondents are asked to answer each statement simply in terms of *how often* they feel or behave in the stated manner.

#### Mindful Attention Awareness Scale

The Mindful Attention Awareness Scale [41,42] is a 15-item questionnaire that measures mindfulness (ie, nonjudgmental consciousness of the present moment). Each item presents a statement with a 6-point response scale ranging from *almost never* to *almost always*. The respondents are asked to what degree each statement pertains to their *current experience*.

#### Health and Work Performance Questionnaire Scales (Employee Version)

Two sections from the employee version of the World Health Organization Health and Work Performance Questionnaire [43]—scale B9 and scale B12—will be used to measure work performance. Scale B9 contains 5 items asking how many days in the past 4 weeks the respondent missed an entire workday, missed part of a workday, or performed extra work outside their usual working hours. Scale B12 contains 7 items about the respondent’s work performance in the past 4 weeks (referring to both overperformance and underperformance), with a 5-point response scale ranging from *none of the time* to *all of the time*.

#### Utrecht Work Engagement Scale

The Utrecht Work Engagement Scale [44] is a 17-item questionnaire that measures the respondent’s level of engagement with their work (eg, *I am enthusiastic about my job*). Each item presents a statement with a 7-point response scale ranging from *never* to *always/every day*.

#### Daily Life Events

The Daily Life Events (DLE) scale [45] is a list of minor and major positive and negative life events, and the respondents are asked whether each event has happened to them and, if so, whether it has had a positive, neutral, or negative impact on them. For this study, we used the trauma items from the original DLE scale and adapted the other items to be answered in reference to COVID-19. The trauma section lists 7 potentially traumatic life events (eg, being physically or sexually assaulted) and asks the respondents whether each event has ever happened to them and, if so, how many years ago it last occurred. The COVID-19 section lists 15 life events (eg, separation from family and working from home) and asks the respondents whether each event has happened to them in the last 12 months (ie, during the COVID-19 pandemic) and, if so, how many months ago it last occurred and whether it had a positive, neutral, or negative impact on them, with a 7-point response scale ranging from −3 (*extremely negative impact*) to +3 (*extremely positive impact*). The DLE scale is provided in Multimedia Appendix 1.

#### COVID-19 Exposure Survey

The COVID-19 Exposure Survey is a compilation of items regarding the impact of the COVID-19 pandemic on the respondents and their workplace (ie, their ward at the hospital). The survey includes questions on how many times the respondent has been tested for COVID-19, whether they have contracted the virus, whether they have had to care for a patient with the virus, whether the pandemic has affected their workload, and whether they have considered leaving their job during the pandemic. The COVID-19 Exposure Survey is provided in Multimedia Appendix 1.

#### Thrive Program Attendance and Satisfaction Survey

This survey asks the respondents which of the 2 versions of the Thrive program they received (this question will serve as a manipulation check), how much of the program they have completed (ie, their attendance), whether they enjoyed it, and how helpful they felt it was for both themselves and their patients. This survey will be administered only after the Thrive program has concluded (ie, in weeks 8 and 12); however, items 7 and 8 of the survey (Multimedia Appendix 1) will be administered in week 4 to measure attendance up to that point. When item 8 is administered in week 4, it will ask about attendance only for weeks 1 to 3. When administered in weeks 8 and 12, this item will ask about attendance across all 7 weeks of the program.

### Primary and Secondary Outcomes

The primary outcomes for this RCT will be the participants’ levels of well-being (as measured by the COMPAS-W) and their levels of psychological distress (as measured by the Depression, Anxiety, and Stress Scale–21-item version). Thus, the primary outcomes will encompass both dimensions of mental health: mental well-being and mental illness. The secondary outcomes will be health and lifestyle habits, mood states, compassion (for oneself and others), mindfulness, work performance, and work engagement. Program attendance, resiliency resources, medical history, trauma, coping styles, and pandemic-related variables will serve as potential moderator variables along with demographic variables such as age, sex, ward, and occupation. The primary end point for the analysis will be the third measurement occasion (week 8), and the secondary end points will be the second and fourth occasions (week 4 and week 12).

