**Objective:**

This paper describes the protocol for a randomized controlled trial whose objective is to evaluate the Thrive program in comparison with an active control condition to measure whether the program is effective at increasing well-being and decreasing symptoms of psychological distress in health care workers at a designated Australian hospital.

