This paper outlines the protocol for an RCT evaluating the effects of a new well-being program—the *Thrive* program—for health care workers at a large public hospital in metropolitan Sydney, New South Wales, Australia. Thrive is a web-based psychoeducational program that provides information and guidance within seven areas of life related to mental well-being: sleep, exercise, nutrition, stress management, social connection, cognitive challenge, and life purpose. The program is innovative in that it covers how these 7 aspects of life affect not only well-being in general but also brain health in particular. With advances in neuroscience and neuroimaging in the 21st century, there is now a sufficient knowledge base to underpin this specialized intervention, which is aimed at promoting well-being via healthy habits and lifestyle decisions that directly affect the organ on which mental health ultimately depends—the brain. Another key strength of this study is that the COMPAS-W well-being scale [4] will be used as the primary outcome measure, allowing for a comprehensive assessment of the participants’ subjective and psychological well-being and an opportunity to detect whether one or more of the 6 subcomponents of well-being is more or less responsive to the intervention. To the authors’ knowledge, this will be the first intervention for health care workers to use an empirically derived measure of well-being that has also been validated with regard to genetic [7,26-28] and neural [5,6,29] markers as well as psychological factors, including resilience, trauma, and coping strategies [30,31].

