### Objectives

This study has 2 main objectives. First, it aims to determine whether the Thrive program results in significant gains in well-being—as measured by the COMPAS-W scale—in the intervention group compared with an active control group and, if so, which of the specific COMPAS-W subcomponents is most responsive to the program. Second, from the baseline measurements, the study will inform researchers, hospital staff, and other stakeholders of the current levels of overall mental health and well-being among the health care workers at the target hospital.

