### Analysis

Missing values in the data set will be estimated via multiple imputation, and the initial analyses will be conducted on an intention-to-treat basis followed by per-protocol analyses to account for levels of treatment compliance (eg, program attendance). The data will be analyzed via a linear mixed model that will allow the group-by-time interaction effects to be estimated. It is hypothesized that levels of well-being will increase over time in the intervention condition relative to the active control condition. Similarly, it is hypothesized that levels of psychological distress (ie, symptoms of depression, anxiety, and stress) will decrease over time in the intervention condition relative to the active control condition. There may also be a group-by-time interaction effect on one or more of the secondary outcomes. For example, the intervention may promote increased compassion, mindfulness, or work engagement. Furthermore, any interaction effect may itself be moderated by a variable such as resilience or coping style (cf [9,31]).

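### The article names one primary outcome in its Introduction and two in its Methods, sizes a single test at 0.05, and does not say whether one or both must succeed

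*Protocol article*

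**What the plan says.** The sections of the protocol article describe the primary question in two ways.

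**One outcome.** The end of the Background section states that "the COMPAS-W well-being scale [4] will be used as the primary outcome measure". The Objectives section then gives two main objectives. The first concerns effectiveness and is confined to "gains in well-being—as measured by the COMPAS-W scale—in the intervention group compared with an active control group"; it goes on to ask which subcomponent responds most, but only if there is an overall gain. The second is a description of baseline mental health. Distress is not part of the effectiveness objective.

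**Two outcomes.** Primary and Secondary Outcomes uses the plural and lists "levels of well-being (as measured by the COMPAS-W) and their levels of psychological distress", with the DASS-21 as the measure of the second. It explains the pair as covering both sides of mental health, and it sets week 8 as the primary end point. The Abstract's objective also pairs them, asking whether "the program is effective at increasing well-being and decreasing symptoms of psychological distress in health care workers". The Analysis section states one hypothesis for well-being and a second, that "levels of psychological distress (ie, symptoms of depression, anxiety, and stress) will decrease over time in the intervention condition".

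**Error rate and power.** The only alpha in the article is the 0.05 in Sample Size. It is used for one group-by-time interaction: partial eta squared 0.01, correlation 0.5 among repeated measures, 80% power, 69 per group, raised to 99 per group for 30% attrition, with a target of at least 200 in total. No section splits that alpha, orders the two outcomes, or says whether one or both must succeed.

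**The concern.** Someone working from the Background and Objectives would treat a benefit on DASS-21 alone as a secondary result. Someone working from the outcomes section could report it as a primary success. The article supports both.

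The choice affects what the trial may conclude. If either outcome can carry the claim at 0.05, the error rate for the primary claim exceeds 5%. If both are required, the 80% power no longer describes the chance of a primary success. The 0.05 and 80% apply to the primary claim without further adjustment only if there is one primary outcome, and the outcomes section does not say that.

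Timing adds to the need to settle it. According to the Results section, the first cohort completed its fourth survey in May 2021, and staff of the remaining wards are invited from October to December 2021. Some outcome data therefore exist while the primary claim is worded two ways. The article does not say that anyone has analysed them.

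**Working it through.** **Inputs from the Design and Sample Size sections.** Groups k = 2, occasions m = 4, correlation among repeated measures 0.5, partial eta squared 0.01, alpha 0.05, power 80%, attrition 30%.

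**Assumed input.** The correlation r between the COMPAS-W and DASS-21 test statistics is not given. The range 0 to 0.8 is used, with DASS-21 scored so that benefit points the same way on both.

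**1. The plan's own figure.** For the within-between interaction F test with no sphericity correction:

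- f² = 0.01/0.99 = 0.0101
- noncentrality = f² × N × m/(1 − 0.5) = 0.0101 × N × 8
- df1 = (k − 1)(m − 1) = 3; df2 = (N − 2) × 3

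N = 136 gives 79.9% power. N = 138 (69 per group) gives noncentrality 11.15, df2 = 408 and 80.6% power. Attrition: 69/0.70 = 98.6, so 99 per group. Both stated figures are reproduced, and they are for one test at 0.05.

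**2. Either outcome suffices, 0.05 each.** If independent, 1 − 0.95² = 0.0975. For correlated two-sided z tests the result is 1 − P(|Z1| < 1.96 and |Z2| < 1.96):

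| r (assumed) | Chance of at least one false positive |
|---|---|
| 0 | 9.75% |
| 0.5 | 9.1% |
| 0.7 | 8.3% |
| 0.8 | 7.8% |

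Whatever the correlation, two tests at 0.05 cannot exceed 10%.

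**3. Both must succeed, each with 80% power.** If independent, 0.80 × 0.80 = 0.64. With correlation, a bivariate normal approximation with 80% in each margin gives:

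| r (assumed) | Joint power |
|---|---|
| 0 | 64% |
| 0.5 | 69% |
| 0.7 | 71% |
| 0.8 | 73% |

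**4. Either suffices, alpha split to 0.025 each.** The family-wise error if independent is 1 − 0.975² = 4.94%. The expected completers are 200 × 0.70 = 140. At N = 140, power per outcome is 81.2% at 0.05 and 72.7% at 0.025. Restoring 80% at 0.025 takes N = 162 (81 per group); 81/0.70 = 115.7, so 116 per group, or 232 recruited.

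**5. COMPAS-W alone.** No split is needed, and the alpha and sample size of the Sample Size section stand as written.

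These steps take the stated interaction power as the power for each outcome. They do not examine whether it also holds for a contrast at week 8 alone.

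**The case against.** The strongest reply is that this is one loose sentence against a clear Methods statement. Only the Background uses the singular label, in a sentence about the strengths of the scale; the Objectives section never uses the word primary. The Abstract, the outcomes section and the Analysis section all cover both outcomes, and the outcomes section gives a reason for the pair and fixes the time point. On this view the design has two primaries, and how their error rate is handled belongs in an analysis plan that is not shown.

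Much of that stands, and it rules out several stronger readings that a reader might draw:

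- *That the primary claim is undefined.* It is inconsistently described; the instruments and the primary week are stated.
- *That each hypothesis will be tested at an unadjusted 0.05.* The article gives no test level for the analysis. The 0.05 is a sample-size assumption, so the 8-10% is conditional on either-can-win testing at that level.
- *That the false-positive risk reaches about 19%.* That needs four independent primary tests (1 − 0.95⁴ = 18.5%), with the three DASS-21 subscales each primary. The outcomes section names DASS-21 once, as psychological distress, and the symptom list in the Analysis section repeats what the instrument measures. Independence also sits badly with the Background, which reports that higher well-being went with lower depression, anxiety and stress.
- *That the six COMPAS-W subcomponents are further routes to primary success.* The Objectives section makes that question conditional on an overall gain.

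The reply does not remove the contradiction. The effectiveness objective leaves out an outcome that the Methods call primary, and an analysis plan cannot make those sections agree. Nor does it remove the mismatch with the sample size: the calculation provides for one test, and both two-outcome rules examined above, an alpha split or a both-must-succeed rule, cost power that the article does not acknowledge.

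**Conclusion.** The concern holds as an inconsistency that should be corrected before the full data are analysed. The article describes the primary question as one outcome in its Introduction and two in its Methods, sizes one test at 0.05, and gives no success rule.

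Its size depends on the rule that is meant: a false-positive rate of about 8-10% if either outcome suffices at 0.05, or joint power of about 64-73% if both must succeed and each has 80%. Both ranges rest on assumed correlations of 0 to 0.8 between the two tests. If COMPAS-W is the only primary outcome, neither cost arises.

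**What to change.** Make the Background, Objectives, Sample Size, Primary and Secondary Outcomes, and Analysis sections agree, before the full data are analysed.

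**Simplest option.** Name the COMPAS-W overall score at week 8 as the sole primary outcome. Test DASS-21 overall distress at week 8 next, at 0.05, only if COMPAS-W is significant. Label the COMPAS-W subcomponents and DASS-21 subscales supportive. This holds the error rate for the two outcomes at 5% and leaves the alpha and numbers in Sample Size unchanged. The overall score would have to be written in: neither the Background nor the Objectives section specifies it, and week 8 appears as the primary end point only in the outcomes section.

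The cost is more than wording. A DASS-21 claim would depend on COMPAS-W succeeding first. A declared primary outcome would move to second place after registration (January 2021) and after the first cohort's final survey, so the change should be dated and recorded, with a statement of whether any outcome data had been examined.

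**If two primaries are kept.** State the success rule and restate the power:

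- Either suffices, with 0.025 each: about 73% per outcome with 140 completers, or 232 recruited to restore 80%.
- Both must succeed: no alpha split is needed, but joint power is about 64-73% if each outcome has 80%.

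In either case the Background and Objectives should then name distress alongside well-being.

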### Procedure and Materials

#### Intervention

The intervention participants will receive the full version of the Thrive program, comprising a 1-hour web-based presentation each week for 7 weeks. Each presentation will be a webinar (web-based seminar) delivered via the Zoom platform (Zoom Video Communications Inc). Participants will view the webinars as prerecorded videos on a dedicated webpage, which will ensure uniform delivery of the intervention. Each webinar will be copresented by 2 members of the research team. One presenter (MM) is a Nurse Educator from the hospital with a Master’s degree in Adult Education and extensive experience in providing professional development courses to health care workers. The other presenter ([name]) is a researcher from the [name] Group at Neuroscience Research Australia (NeuRA) and the University of New South Wales (UNSW) with a PhD in Psychology and extensive experience in lecturing, tutoring, and counseling.

Each webinar will follow a 3-step sequence named *Inform, Inspire, Improve*. The *Inform* and *Inspire* sections will last approximately 25 minutes each, and the *Improve* section will last approximately 10 minutes. During the *Inform* section, the presenters will share scientific findings from the fields of neuroscience, medicine, and psychology to educate the participants on the links among brain health, mental well-being, and one of the 7 areas of life covered by the program. This section will provide knowledge only, as a background to the subsequent sections. During the *Inspire* section, the presenters will provide advice, guidance, and recommendations on how to improve one’s brain health and mental well-being in the relevant area of life. This section will build upon the preceding knowledge by offering practical suggestions to implement in one’s daily life. Finally, during the *Improve* section, the webinar viewers will have an opportunity to reflect on the knowledge and suggestions shared in the preceding sections, and they will be invited to commit to enacting at least one of the suggestions in their own lives.

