**Webinar topics and content**
Week 1 (sleep): impact of sleep quantity and quality on well-being and the brain; tips for improving sleep quality in relation to light exposure, exercise, meal timing, and nutrition; cognitive behavioral tips for sleeping better; and accessing treatment for a sleep-related disorderWeek 2 (exercise): impact of physical activity on well-being and the brain; tips for increasing motivation to exercise in relation to social connection, natural environments, and novelty or variety; using the internet to find new ways to exercise; exercising in a way that suits one’s personal preferences; and how to access an exercise physiologist through the publicly funded health care systemWeek 3 (nutrition): impact of nutrition on well-being and the brain; links among nutrition, human evolution, and chronic noncommunicable diseases; tips for improving one’s diet in relation to avoiding empty calories, practicing mindful eating, and accommodating dietary restrictions; and how to get tested for micronutrient deficienciesWeek 4 (stress management): impact of stress on well-being and the brain; how the stress system works; tips for managing and reducing stress using mindfulness, controlled breathing, and effective coping strategies; and how to access treatment for posttraumatic stress disorder or a stress-related disorderWeek 5 (social connection): impact of social connections on well-being and the brain; tips for improving connections using compassionate communication, active listening, nonverbal communication, and acts of kindness; and how to use the internet to make new social connectionsWeek 6 (cognitive challenge): impact of cognitive challenge on well-being and the brain; tips on challenging oneself using new knowledge, linguistic or mathematical puzzles, skill development, and novelty; and how to overcome anti-intellectual stigma and follow one’s curiosityWeek 7 (life purpose and meaning): impact of life purpose on well-being and the brain; the differences between hedonia and eudaimonia; the state of flow and how to achieve it; and tips for achieving a greater sense of purpose and fulfillment by targeting character strengths and weaknesses, setting meaningful goals, accepting unavoidable hardship, and identifying one’s core values

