#### Active Control

The active control participants will receive an extremely reduced version of the Thrive program. In each of the 7 weeks, they will be emailed the infographic summary on that week’s topic and instructed to read it. The infographic documents will be identical to those received by the intervention participants. In short, the control participants will be provided with only the *Inform* section for each week’s topic, in the form of the infographic summary only. They will not receive any tips and advice for promoting well-being. Thus, the intervention participants will receive knowledge plus practical advice and reflective opportunities (in webinar and document forms), whereas the control participants will receive knowledge only (in document form only). The control participants will receive a reference list to accompany each infographic summary, but they will not receive the reflective sheets. To summarize, each week, the intervention participants will receive a webinar, reflective sheet, infographic, and reference list, whereas the active control participants will receive the infographic and reference list only.

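### Attendance, known only after randomization and different in kind by arm, is planned as a moderator and as the basis of per-protocol analysis, so these secondary comparisons are not randomized

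*Protocol article*

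**What the plan says.** All references are to the protocol article.

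- **Moderators.** Primary and Secondary Outcomes states that "Program attendance, resiliency resources, medical history, trauma, coping styles, and pandemic-related variables will serve as potential moderator variables", together with demographic variables. Analysis adds that "any interaction effect may itself be moderated by a variable such as resilience or coping style".
- **Order of analyses.** Under Analysis, "the initial analyses will be conducted on an intention-to-treat basis", "followed by per-protocol analyses to account for levels of treatment compliance (eg, program attendance").
- **How attendance is obtained.** The attendance and satisfaction survey asks respondents "how much of the program they have completed (ie, their attendance"). Table 1 places the attendance items in surveys 2, 3 and 4 only (weeks 4, 8 and 12). The week-4 item covers program weeks 1 to 3; the later ones cover all seven weeks.
- **What there is to attend.** The intervention is described as "comprising a 1-hour web-based presentation each week for 7 weeks". Of controls, Active Control says that "they will be emailed the infographic summary on that week’s topic and instructed to read it".
- **Coping.** Table 1 gives the Brief COPE at all four surveys, including week 0. The week-4 webinar includes "tips for managing and reducing stress using mindfulness, controlled breathing, and effective coping strategies".

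**The concern.** A moderator of a treatment effect has to be fixed before treatment can influence it. Resilience, trauma and medical history are background traits collected at week 0 only. Attendance stands in the same list but has no pre-randomization value, so no later definition could turn it into a baseline effect modifier.

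The per-protocol analysis meets the same difficulty. Sitting through seven hours of webinars and reading seven short documents are different demands, so those who count as compliant in one arm need not resemble those who count as compliant in the other. If people who are faring better are likelier to keep watching, compliant webinar participants will look better than compliant readers even if the program does nothing. The same mechanism yields a group-by-attendance interaction, which is easily taken for dose-response.

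Low engagement is a live possibility. Background cites a comparable web-based trial in which 9 of 178 intervention participants took part in the activities (9/178 = 5%).

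**Working it through.** **1. The plan's own figure.** Sample Size gives partial eta-squared 0.01, alpha 0.05, correlation 0.5 and 80% power; the design has two groups and four occasions.

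- f² = 0.01/0.99 = 0.0101.
- λ = f² × N × 4/(1 − 0.5). At N = 138, λ = 0.0101 × 138 × 8 = 11.15.
- With 3 and 3 × (138 − 2) = 408 degrees of freedom, power is 0.806. N = 136 gives 0.799.
- So 138 in total, 69 per group; 69/0.70 = 98.6, rounded up to 99.

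The stated figures reproduce and this point does not affect them. They supply the group sizes used below: 69 (completers) and 100 (recruits).

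**2. Null simulation.** There were 3,000 trials per setting, with no effect of assignment on the outcome. The week-8 score was regressed on baseline and group. Outcome SD is 1 and the baseline to week-8 correlation is 0.5, as in Sample Size. The rest is assumed, because the documents give no attendance rates:

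- an unmeasured post-baseline factor U explains 25% of the residual outcome variance;
- about 50% attend in the webinar arm and 80% in the reading arm, except in the last row;
- U shifts the log-odds of attending by the slope shown, per SD of U.

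Rejection rates at the 5% level are given as 69 per group / 100 per group:

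| Slope: webinar, reading | ITT | Per-protocol | Mean spurious per-protocol effect (SD) | Group-by-attendance |
|---|---|---|---|---|
| 0, 0 | 4.1 / 5.0% | 4.6 / 4.8% | 0.00 / 0.00 | 4.6 / 5.1% |
| 0.5, 0 | 4.8 / 4.6% | 7.9 / 10.7% | 0.10 / 0.11 | 8.6 / 11.6% |
| 1.0, 0 | 4.7 / 5.4% | 15.4 / 20.7% | 0.18 / 0.18 | 19.3 / 26.9% |
| 1.5, 0 | 5.0 / 4.7% | 22.7 / 31.0% | 0.23 / 0.23 | 27.7 / 38.7% |
| 1.0, 1.0 | 4.3 / 5.4% | 7.1 / 8.9% | 0.08 / 0.09 | 5.3 / 4.7% |
| 1.0, 1.0; 50% attend in both | 4.9 / 5.2% | 4.7 / 5.5% | under 0.01 | 4.8 / 5.5% |

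Simulation error at a true 5% is √(0.05 × 0.95/3000) = 0.4 percentage points. The false-positive rate rises with sample size because the bias does not shrink while the standard error does. The model is simpler than the planned one: a single week-8 comparison, complete data and a yes/no attendance variable.

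**3. Coping.** In the same set-up, the group term was tested in a model that also held week-8 coping and its interaction with group. The test kept about 5% when the program did not change coping. It rejected in 7% of trials when coping shifted by 0.3 SD, and in 12% to 14% when it shifted by 0.5 SD. A coping score that assignment has not changed produces no inflation.

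**The case against.** Intention-to-treat comes first, and per-protocol as a follow-up is a common sequence. Moderators are only called potential, and how per-protocol will be defined may properly sit in an analysis plan that is not shown. All this is fair. It limits the point to secondary analyses, and the missing definition is not held against the article. It does not rescue attendance as a moderator, because the article itself fixes when attendance is measured.

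A second objection is that the bias may be zero. That also stands: the first and last rows of the table show it. But the last row needs the same selection and the same attendance rate in both arms, and nothing in the documents makes that likely when the two tasks differ so much.

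Two stronger readings are tempting.

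- **Coping.** A reader might infer that post-randomization coping scores will be used as moderators, since coping is measured four times and taught in a webinar. The text does not say so. A week-0 score exists, and Background describes the earlier trial cited for this moderation as finding it in those with low resiliency resources at the outset, which suggests baseline values. This is a clarification to make, not a stated error.
- **A fixed bias.** A reader might take the mean shift among compliers as the bias. If 50% comply and compliance propensity correlates 0.3 with the outcome, the shift is 0.798 × 0.3 = 0.24 SD. But that is a one-arm, unadjusted shift. If the propensity correlates equally with baseline, adjustment at a slope of 0.5 leaves 0.24 − 0.5 × 0.24 = 0.12 SD, and a change score leaves zero, before any offset from selection among controls.

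**Conclusion.** The point holds for attendance, both as a moderator and as the basis of the per-protocol analysis. Each conditions on behaviour after assignment that differs in kind between arms, is known only by self-report, and is unreported by those who skip the later surveys. With no true effect and selection confined to the webinar arm, false-positive rates were about 8% to 31% for per-protocol and 9% to 39% for the attendance interaction across the two sample sizes, with spurious per-protocol effects of 0.10 to 0.23 SD. Those ranges depend on assumed attendance rates and selection strength, and the documents allow no firmer figure.

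A reader might go further and conclude that the trial's main result is compromised. The documents do not support this: the intention-to-treat comparison precedes these analyses, and its simulated error rate stayed at 4.1% to 5.4%. The point should be settled before results are seen, because it governs how the compliance and moderator findings may be read.

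**What to change.** 1. **Moderators.** Remove attendance from the list. State that moderators measured repeatedly (coping, COVID-19 items) enter at their week-0 values. Note that survey 1 follows the email disclosing allocation (Randomization and Informed Consent), so week-0 values precede the program but not knowledge of the assigned condition.
2. **Compliance.** Make a complier-average causal effect, with assignment as the instrument, the main compliance analysis. The design suits it: controls get the full program only after all four surveys, and both arms receive the same infographics. State its assumptions:
   - assignment acts only through the webinar package, including the reflective sheets that controls do not receive;
   - content is not shared between arms, which the plan discourages but cannot exclude;
   - attendance is defined by a stated threshold, and any benefit below it breaks the previous assumption of no other pathway;
   - missing self-reported attendance is handled by a stated method, with a sensitivity analysis.
3. **Per-protocol.** It may stay as a supplement, labelled exploratory and non-randomized. The same label should go on any description of outcomes by attendance.

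The cost is a few sentences of plan text and one further analysis of data already being collected. The downside is precision and reliance on those assumptions. Under one-sided non-compliance the estimate is the intention-to-treat effect divided by the share attending. At an assumed 50% attendance its interval is about 1/0.5 = 2 times as wide as the intention-to-treat interval.
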